## **Title: Implementing a telemedicine and remote-mentoring platform to provide integrated noncommunicable disease and COVID- 19 care in primary care facilities in rural Pakistan**

**1. Background:** The World Health Organization (WHO) recently summarized gaps of COVID-19 challenges, including lack of a national plan to confront and control the pandemic, poor health financing, politicizing proven infection control strategies; and non-optimal use of telemedicine for supporting practices. The report also states challenge of effective control of non-communicable diseases (NCDs) during the pandemic in low-and-middle-income countries (LMICs). People with diabetes and hypertension are older, often over-weight, and have different comorbidities. They are at greater risk of severe complications from COVID-19, but on the same time they require continuous care, which has now been made more difficult due to infection control and social distancing measures at health facilities. A WHO survey in May 2020 showed that over half of its 155 member countries had disrupted hypertension, diabetes treatment and cardiovascular emergencies. Majority of countries responded that staff for routine health programs such as NCDs were partially or fully reassigned to support COVID-19.

Telemedicine and virtual care including telephone and video consultation on mobile phones, have been used as tools to ensure continued health care globally during the COVID pandemic. Even before the COVID-19 pandemic, many have emphasized that digital health tools are important for the prevention and management of NCDs as digital health tools play an essential role in integrated care, especially in managing multimorbidity delivering precision medicine, and increasing medication adherence. WHO reported that 58% countries began to adopt telemedicine in their NCD services, but the evidence is mostly reported from US, China and Iran. The most common forms of telemedicine were phone calls and social media platforms, with some been connected to electronic medical records (EMR). Telemedicine is an effective strategy in reducing exposure to COVID, nosocomial and community transmission, and is acceptable to health providers and patients. However, most primary care providers in LMICs lack the capacity to develop qualified telemedicine platforms. Only a small proportion (5%) of patients with diabetes in India used telemedicine (i.e., simple calls) during the lockdowns, but their response was overwhelmingly positive. Primary-level screening services, delivered through fixed/mobile primary healthcare clinics, community health workers or health campaigns and mobile consultations were identified by health workers, managers and community residents for hypertension in Kenya and Nigeria.

**Pakistan** ranks 7th globally amongst countries with the highest number of persons living with diabetes and hypertension. It has gone through three significant COVID waves and is currently into its fourth wave. Patients with diabetes and hypertension in Pakistan are inadequately managed, as evidenced by high rates of vascular complications and low blood pressure (BP) control rates (30%). Pakistan responded to the COVID epidemic with a lockdowns and focused on hospital-based inpatient care for those with severe symptoms, a strategy that would not reduce community transmission, as shown in other countries. Pakistan also saw a disruption in access to routine care with outpatient visits in **Rural Health Centres (RHCs)**, i.e., the rural public primary facilities, declining by 40% in June 2020.

According to Pakistan Telecommunication Authority, there are 185 million mobile connections (84% tele-density) in Pakistan among a total population of 225 million; and around half of these connections are smart phone users. The internet broadband subscribers stand at 104 million with a penetration of 48%. With a digitalization at an early stage especially in rural areas, Pakistan has seen several telemedicine and mHealth initiatives piloted by organizations such as COMSTATS, and Aga [name] University Hospital Karachi. COMSTATS has established telehealth clinics in isolated areas to provide easy access to healthcare for the most vulnerable population of the country. However, none of them has been able to sustain and successfully scale to a large population.

Though unprecedented progress has been made in vaccine development, future of the pandemic remains uncertain given that the majority of LMIC population will not be vaccinated in the several years, while new SARS-COV-2 variants are emerging rapidly. The pandemic is likely to become endemic for years to come in LMICs. Many countries are working on strategies to minimize the COVID-19 transmission and provide vaccination. Pakistan does not have the resource to fully vaccinate its entire population. Therefore, there is an urgent need to strengthen primary care to screen, triage and manage NCDs and at the same time to provide home and community-based solutions to prevent community

transmission of COVID. In the context, care for patients living with diabetes/ hypertension must address their COVID needs, while continuing NCD care with minimal transmission risk. This needs increased skills of health providers in identification and diagnosis of NCD cases and improved triage, diagnosis, treatment and referral services for NCD in intervention population. A remote training and monitoring platform is equally important to maintain high quality of care in LMICs. Our previous studies demonstrated the feasibility and effectiveness of a community-based hypertension/ diabetes management in Pakistan. The Extension for Community Healthcare Outcomes (ECHO), a remote training and mentoring system, was proved effective to improve NCD management. We have successfully conducted online training of COVID-19 in primary healthcare facilities in Asia and Africa. There is a high need in LMICs for evidence regarding the feasibility and effectiveness of an integrated COVID-NCD prevention and care that is guided by implementation science frameworks.

**2. Hypothesis, Aims and Objectives:** We aim to design a package of integrated Covid-NCD care in RHCs of Punjab Province, Pakistan. Based on our existing NCD projects in Punjab, we will adapt our COVID-19 primary care guidelines developed in other LMICs, to integrate COVID-19 vaccination, health education, case management and support for patients with hypertension/ diabetes. Our study is guided by the implementation science RE-AIM framework, which tackles health system factors at multiple levels. Our overall aim is to reduce patient overload at hospitals, avoid nosocomial transmission, reduce community transmission, and provide patient support.

**Specific objectives** include: 1) to conduct a rapid context analysis at primary care level by focusing on issues relating to how to embed COVID-19 care into the existing NCD programs in RHCs; 2) to evaluate the effectiveness of the integrated COVID-NCD care package based on clustered randomized controlled trial; 3) to conduct process evaluation and cost-effectiveness analysis that is embedded in the project to facilitate future scaling up the evidence in Pakistan and other LMICs; 4) to plan, prepare for scale-up the package in Pakistan and other LMICs.

#### **4. Study Phases and Methods**

**4.1 Study Settings:** The Province of Punjab, Pakistan, has 110 million inhabitants in 36 districts; about two-third of the population live in rural areas. The rural population is served mainly by a network of more than 315 RHCs, and 120 district level hospitals. Each RHC provides primary care to a catchment population of 200,000 rural inhabitants. RHC staff includes: 1) three or more doctors; 2) five or more allied health workers including paramedics, lady health visitors, nurses, dispenser, laboratory technician; and 3) support staff. Currently, the research team in Pakistan ASD is leading the WDF project in 84 RHCs among 10 districts in Panjab. The WRF project have diagnosed and are providing treatment to 10,000 patients with diabetes or hypertension. Currently, no Covid-19 care or prevention is provided in RHCs. Testing is only provided at the district hospital which is remote to most patients.

**4.2 Phase I: Context analysis and intervention design (objective 1), 3 months:** We will mainly use document review and qualitative study to understand the impact of the pandemic, assess bottlenecks, any resilience of the system that helps tailor possible approaches. This will be conducted in 2 RHCs based on their level of performance (good or not-well) as recommended by ASD, one as intervention and another as control. Based on this, we will develop the interventions.

Study methods including:

- 1) document review: to review current NCD-COVID care under the routine WDF project, and existing national and global guidelines for hypertension, diabetes and COVID care.
- 2) stakeholder meetings: with relevant government health decision makers, NGOs and patients, healthcare providers at RHCs to assess the current state of hypertension and diabetes prevention and care, and to share objectives and components of study interventions.
- 3) key informant interviews: We will conduct in-depth interviews with key stakeholders. These are likely to include leaders, policymakers, health providers from RHCs, the district, and community. We will explore the structural, organisation, provider and patient factors that may determine NCD care implementation, and how NCD care is affected/interrupted by the pandemic. We will also explore how sex and gender factors such as cultural factors, as well as gender-based inequities or barriers to care, are relevant in current NCD care under the pandemic. Exact numbers of interviews will be decided based on further understanding of the context. Phase 1 will also be used for ethics approval, modifications of sample size estimation and staff recruitment for phase 2 if necessary. If the interventions are not to be revised substantially, these two pilot sites will serve in the trial (internal pilot).

#### **4.3 Phase II: Implementation and Evaluation (objective 2-3), 12 months implementation:**

We will conduct a parallel two-arm, cluster randomized controlled trial of the enhanced NCD-COVID-19 integrated care package in rural Punjab, Pakistan. The Province of Punjab has 110 million inhabitants in 36 districts; about two-third of the population live in rural areas. The rural population is served mainly by a network of more than 315 rural health centers (RHCs), and 120 (sub)district level hospitals. Each rural health centre provides primary care to a catchment population of 200,000 rural inhabitants. The staff of RHC includes: 1) three or more doctors; 2) five or more allied health workers including paramedics, lady health visitors, nurses, dispenser, laboratory technician; and 3) support staff. RHCs offer diagnostic and treatment services for communicable diseases, obstetric and neonatal care, child health, malnutrition and NCDs. The Directorate General Health Services Punjab has already scaled integrated diabetes-hypertension care at the district hospital level, including diagnosis, treatment, lifestyle counselling and reporting tools – using a package of care developed with ASD and Leeds. Currently, ASD is leading the WDF project in 75 RHCs among 10 districts in Punjab to offer NCD care which is focused on diabetes-hypertension diagnosis and treatment.

**4.3.1 Randomization and blinding:** We will recruit and randomize 30 out of the 75 RHCs which currently offer hypertension-diabetes care. RHCs, stratified by district, will be randomly allocated into

intervention and control at 1:1 ratio. RHCs will not be blinded due to the nature of the intervention. To mitigate the risk of bias, we will: 1) mask the statistician and the Data Safety Monitoring Board (DSMB) when data is presented and analyzed; and 2) employ objective outcomes.

**4.3.2 Inclusion and exclusion criteria:** We will invite all clinically diagnosed persons living with hypertension (SBP > 140 mmHg or DBP > 90 mmHg) who 1) reside in the selected RHCs, 2) are 25 years or older, 3) and provide informed consent, and 4) have a smartphone or can access to a smartphone from a relative..

**4.3.3 Our usual care** will be enhanced care under the WDF project, where the NCD (hypertension/ diabetes) care package is implemented. The WDF project provides Zoom-based training of NCD care to RHC staff, but not telemonitoring and mentorship. The NCD care is delivered through outpatient consultations where patients must visit RHCs to get screened, diagnosed, registered, and treated. Since August 2020, regular visits to RHCs have been largely resumed. Medicines are provided freely in RHCs or purchased from private pharmacies if not available. Patients are referred to district hospitals for cardiovascular disease or COVID diagnosis if suspected. Under the usual care, patients with diabetes/hypertension are required to visit RHCs every month and have their health records recorded entered in RHC's EMR. None of the components in an enhanced NCD-COVID integrated care-package, neither the telemedicine, the ECHO-based tele-mentoring platform, nor peer support, will be implemented in control facilities.

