below 130/80 mmHg for patients with diabetes. The denominator will be all NCD participants in RHCs. The numerator will be patients with controlled BP, measured at 10 months; 3) random blood glucose (mmol/L); 4) body mass index (BMI); 5) attendance rate to monthly meetings with RHC doctors (face-to-face or digital); We will also measure indicators related with COVID-19: 6) proportion of patients who have had at least two COVID vaccinations; 7) proportion of patients reporting COVID symptoms; 8) proportion of patients who received COVID care (diagnosis, treatment or home support) from RHCs among those reported COVID-19 symptoms; and 9) proportion of participants been admitted in hospitals for any reasons; 10) mortality rate of participants for any reasons during the 10 months of follow up. We will collect blood pressures, blood profile, and patient body weight and height at Month 1 and 10 in the RHCs. Participants will be asked for fasting for 24 hours and provide a blood sample. During the consultation, the RHC doctor will measure the participants' BP using a calibrated electronic sphygmomanometer after 5 minutes of seated rest, and measure body weight and height. Blood samples will be collected and analyzed in RHC according to national guidelines for fasting plasma glucose. We will collect attendance rates using the routine patient treatment cards in RHCs to record both physical and virtual consultations. We will conduct a survey at the recruitment to collect patient demographics, socioeconomics, smoking status, any COVID symptoms of themselves or family members, health service use, and quality of life. The survey will be repeated at Month 10 in the last follow-up to collect COVID-19 vaccination, symptoms and related care utilization.

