#### **4.3.7 What is the planned recruitment rate?**

Each RHC has at least 100 registered patients with hypertension/ diabetes. We anticipate recruiting 50% of them, to generate 50 participants. The recruiting process will take less than two weeks as all are existing patients registered in RHCs.

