#### **4.6 Data collection, management, and analysis**

We will collect patients' demographic and social information, their exact home address, blood pressures, body weight, and height, knowledge, attitude and practice (KAP) regarding NCD and COVID at the randomization and Month 10 in the RHCs. The RHC doctor will measure the participants' blood pressure using a calibrated electronic blood pressure apparatus after 5 minutes of seated rest, and measure body weight and height. Participants will be asked to provide a blood sample in the RHC at the recruitment and Month 10. In addition, we will also collect patient blood pressures in Month 10 using same methods. Blood samples will be collected and analyzed in RHC according to national guidelines for fasting blood glucose. We will collect attendance rates using the routine patient treatment cards in RHCs to record both physical and virtual consultations. We will conduct a survey at the recruitment to collect patient demographics, socioeconomics, smoking status, COVID-19 immunization status, health service use, medial, KAPs for NCD and COVID, and health care and related costs. The survey will be repeated at Month 10 in the last follow-up to collection information regarding COVID-19 symptoms and related health care consultation and use. Any deaths that occur in patient group during this period will be assigned a probable cause, as determined by a method called verbal autopsy.

Overall, we will conduct mixed methods evaluation to examine the utility of the NCD-COVID guideline, the platforms and care process to inform acceptability, feasibility, reach, adoption, and implementation related challenges (in Section 5.2).

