**5. Project management:** The investigators will seek ethical approvals from the Research Governance Committees in Canada and Pakistan (if needed). The study will be conducted to protect human rights and dignity of the participants. The study has been designed to minimize the burden of participants and any foreseeable risks in relation with the interventions. Interventions of our care program have no known harms. Starting from the usual care period, all participant patients will receive study information in Urdu and English and be invited to participate in the study by research staff in RHCs. We will collect written consents where feasible. We will collect informed consents from all participants. [name] and [name] will be co-guarantees who have full access to the trial dataset. A trial management unit (TMU) will be established in Islamabad, Pakistan with a trial manager and one staff locally and a research coordinator from UofT. TMU will manage the day-to-day activities of the trial. [name] will be the lead statistician, supported by [name]. External member led DSMC will be established to safeguard the safety and privacy of patients involved, and to ensure that all data are collected according to agreed ethical guidelines, properly stored and only used for research purposes. A trial steering committee (TSC) will be established and led by external members. We will organise teleconference meetings for both the DSMC and TSC at the beginning of the study, and then on quarterly basis. The committees may also meet on an ad hoc basis should the need arise.

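### Consent and baseline SBP are not required before an RHC's allocation is disclosed, and unblinded RHC doctors take the SBP with only a partial device safeguard

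*Protocol*

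**What the plan says.** - **Blinding.** Protocol 4.3.1 says "RHCs will not be blinded due to the nature of the intervention". It lists two mitigations: to "mask the statistician and the Data Safety Monitoring Board (DSMB) when data is presented and analyzed", and to "employ objective outcomes". Section 4.3.8 names the open-label design as a source of bias. It adds no measure against it and refers back to 4.2, although the measures stand in 4.3.1.
- **Recruitment.** Section 4.3.2 invites all eligible patients. Section 4.3.7 starts from at least 100 registered patients per RHC and says "We anticipate recruiting 50% of them, to generate 50 participants", in under two weeks. Section 5 says patients will "be invited to participate in the study by research staff in RHCs".
- **Baseline.** Section 4.3.5 places the first measurements in Month 1. Section 4.6 places them "at the randomization and Month 10 in the RHCs". The primary model in 4.6 adjusts for baseline SBP.
- **Measurement.** In 4.3.5, "the RHC doctor will measure the participants' BP using a calibrated electronic sphygmomanometer after 5 minutes of seated rest"; 4.6 repeats this. Both describe the procedure for the first visit and Month 10. The primary outcome averages SBP taken in the RHC in each of the last three months.
- **Pilot sites.** Section 4.2 names two RHCs, one as intervention and one as control. They may enter the trial if the package is not revised substantially.

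**The concern.** In a cluster trial that enrols individual patients, the main protection against selection bias is to identify and consent them before the cluster's arm is known. If the arm is known first, the decision to join may depend on it, and randomising clusters no longer makes the enrolled patients comparable. The baseline reading has the same weakness. If it is taken with the arm known, the covariate meant to remove chance imbalance can itself depend on allocation.

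Measurement is a second exposure. RHC staff know their arm, and the ECHO training, mentoring and performance monitoring runs only in intervention RHCs (4.3.3, 4.3.4). The doctors who read SBP therefore work under different conditions in the two arms. Masking the statistician and the DSMB happens after these data exist and cannot repair them. The margin is 2.5 mmHg, so a small systematic difference in readings would matter.

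**Working it through.** **1. Order of events.** Four places bear on it.
- 4.3.5 (Month 1) and 4.6 (at randomisation) can both be true, because recruitment takes under two weeks. Neither says whether the baseline reading comes before or after the RHC learns its arm.
- Section 5 has invitation starting from a usual-care period, but the parallel design in 4.3 defines no such period.
- 4.3.1 describes stratified 1:1 allocation and does not say when it is released.
- At the two pilot RHCs of 4.2 the arm is named in Phase I, before enrolment.

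So the order is left open for most RHCs. If the pilot RHCs are kept in the trial with those labels, it is the wrong way round there.

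**2. Measurement.** The device and the rest period limit operator influence. The text does not fix the number of readings per visit, which reading counts or how it is recorded. It describes no procedure or assessor for the two monthly readings before Month 10, although both enter the primary outcome. Averaging three readings reduces random error. A shift common to all three passes through unchanged.

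**3. Size, as an illustration.** Inputs from 4.3.6: margin 2.5 mmHg, SD 11 mmHg, one-sided 5%, power 90%, ICC 0.03, 15 clusters of 40 per arm.
- The plan's individual sample size: n = 2 × (1.645 + 1.282)² × 11² / 2.5² = 332 per group. This matches.
- Design effect: 1 + 39 × 0.03 = 2.17. (332 × 2.17 = 720, not the 614 stated. That is a separate matter; the standard error below does not use 614.)
- Standard error of the difference: 11 × √(2 × 2.17 / 600) = 0.936 mmHg.
- Let b be the net differential error favouring the intervention in the three-month average, after baseline adjustment. If the package is truly worse by the full margin, the chance of declaring non-inferiority is Φ(b/0.936 − 1.645).

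| Assumed b (mmHg) | ICC 0.03 (SE 0.936) | ICC 0.01 (SE 0.749) |
|---|---|---|
| 0 | 5% | 5% |
| 0.5 | 13% | 16% |
| 1 | 28% | 38% |
| 2 | 69% | 85% |

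- In the other direction, with no true difference, power is Φ(2.5/0.936 − 1.645) = 85%. A 1 mmHg error against the intervention gives Φ(1.5/0.936 − 1.645) = 48%.
- Baseline adjustment changes b. If baseline and follow-up readings carry the same error e, the net error is about e × (1 − β), where β is the slope on baseline SBP. With an assumed β of 0.5, reading errors of 1 and 2 mmHg become b = 0.5 and 1, giving 13% and 28%. The full 28% and 69% apply only if follow-up is shifted and baseline is not.

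**The case against.** The strongest reply is that the protocol already does a good deal. It invites all eligible patients, so the 50 per RHC is an expected yield and not a quota filled by choice. The inviters are research staff placed in RHCs, who may not know the arm. SBP is read on a calibrated electronic device under a standard rest condition and averaged over three months.

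Most of this stands, and it rules out several stronger readings that a reader might infer:
- **Unblinded clinic staff hand-pick patients.** Not supported. The inviters are research staff, their masking is unstated, and all eligible patients are invited.
- **The safeguards cover nothing.** Too strong. The electronic device is a real, though partial, safeguard on measurement.
- **Readings are written by hand and rounded favourably.** Not in the text. The recording method is unstated.
- **The doctor who measures is the one who delivers the package.** Likely in places but inferred, since an RHC has three or more doctors.
- **Any bias favours non-inferiority.** Not established. Enrolling less well-controlled patients in the intervention arm would act the other way.
- **Month 1 and randomisation contradict each other.** They need not.

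The reply does not reach the central gap. Inviting everyone does not stop consent from depending on a known arm when about half are expected to join, and nothing puts consent or baseline SBP before disclosure.

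**Conclusion.** The point holds as a gap in conduct that the protocol leaves open, not as demonstrated bias. Three things are established: RHCs are open-label, RHC doctors take SBP at baseline and Month 10, and no section requires consent and the baseline covariate to precede disclosure of allocation. Masking at analysis addresses none of these, and the device addresses measurement in part.

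The documents give no figure for the size of any error. The 13%, 28% and 69% rest on assumed net errors of 0.5, 1 and 2 mmHg favouring the intervention after baseline adjustment, on the planning SD and ICC, and on a true difference equal to the margin. They show how sensitive a 2.5 mmHg margin is and do not predict what will happen. The change is worth making because it is cheap, and because no later analysis can restore the order of enrolment.

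**What to change.** **Main change (4.3.1, 4.3.5, 4.6).** State that in every RHC all eligible registered patients are invited and consented, and have the baseline survey and SBP completed, before that RHC's allocation is released. Use that wording for the timing of baseline in both 4.3.5 and 4.6. State who recruits and whether they are masked. Correct the cross-reference in 4.3.8 to 4.3.1.

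**Pilot RHCs (4.2).** State how the two sites already labelled by arm are handled, for example by leaving them out of the primary analysis or by a sensitivity analysis without them. If both are among the 30, one per arm, and are not replaced, the standard error becomes 0.936 × √(15/14) = 0.968, and power at ICC 0.03 falls from about 85% to Φ(2.5/0.968 − 1.645) = 83%.

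**Secondary change (4.3.5).** Apply one measurement procedure to all three monthly outcome readings in both arms, with a fixed number of readings per visit. Where the device stores readings, use its record as the source. The documents do not say that the devices can do this, so it needs checking. It also would not stop an unblinded operator from affecting the conditions of measurement.

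**Cost.** Allocation release is delayed by about two weeks, the recruitment time in 4.3.7. Device records for baseline and three monthly visits would mean up to 50 × 4 = 200 patient-visits per RHC, or 6,000 in all, with more captures if several readings are taken per visit.
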